## Trial status

Recruitment for the trial is planned to start on June 2021 and last until June 2023. The trial is enrolling patients. The current protocol version is 2.0.

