## Methods/design

### Study design

This study presents a randomized, double-blinded, and placebo-controlled clinical trial performed in accordance with the Declaration of Helsinki, the Standard Protocol Items: Recommendations for Interventional Trials (SPIRIT) 2013 Statement [18], and the Standard Protocol Items for Clinical Trials with Traditional Chinese Medicine: Recommendations, Explanation and Elaboration (SPIRIT-TCM) Extension 2018 Statement [19] from June 2021 to June 2023. In this study, a total of 80 eligible patients will be enrolled and randomly classified into the JLJ granules group or the placebo control group. All the patients voluntarily will sign an informed consent before being included. Each included patient will be numbered in sequence and randomly classified into two groups using a ratio of 1:1. Participants in the JLJ granules group will be instructed to take JLJ granules (110 g per day) for 3 consecutive months, while participants in the placebo control group will be given placebo granules with the same appearance and smell as JLJ granules but no therapeutic effect (110 g per day) for 3 consecutive months. All of the researchers and patients will be blinded right from the beginning of the trial. All the clinical data will be recorded before the intervention (0 week) and after the intervention (at month 3, month 6, and month 12), and the results of the electronic colonoscopy will be recorded at month 12. The proposed project schedule is illustrated as a flowchart in Figs. 1 and 2.

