### Study period

The course of intervention is set as 3 months. Follow-ups will be conducted at months 3, 6, and 12, and clinical data will be recorded again, and the reexamine of colonoscopy will be undergone at month 12. A safety evaluation will be carried out for all the patients after treatment initiation (comprising blood routine, urine routine, stool routine, liver and kidney function, and electrocardiography).

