### Outcomes

#### Primary outcome

The primary outcome of this study is the recurrence rate of CRA within 12 months: refer to the Diagnostic Criteria and Therapeutic Effect for Diseases and Syndromes in Traditional Chinese Medicine (Chinese Medicine Industry Standards of the People's Republic of China; ZY/T001.1–94); recurrence refers to the formation of new adenomatous lesions after complete resection of the initial lesions, appearing at the original affected site or at other sites. The recurrence rate of adenomas = the number of patients with recurrence/the number of intra-group patients × 100%. The size, number, location, pathological type, etc. of CRAs will also be recorded.

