However, there are also several limitations that need to be considered in this study. First of all, due to funding constraints, our follow-up period is only 12 months and we are not able to conduct a long-term follow-up observation. Moreover, the sample size included in the trial is relatively small, and the results may be biased compared with the results of multi-center and large sample size clinical trials. If high-quality evidence for the efficacy, safety, and recurrence rate of JLJ granules in the treatment of postoperative patients with CRA can be provided in this study, a large sample size, multi-center, randomized controlled, and double-blind trial will be conducted in the next step to provide a more reliable basis for JLJ granule administration in the management of postoperative CRA patients, so as to improve symptoms and avoid recurrence.

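### The whole trial and its recruitment window carry the same dates, June 2021 to June 2023, which leaves no room for the month-12 colonoscopy in patients enrolled after about June 2022

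*Protocol article*

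**What the plan says.** All statements are from the protocol article.

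- **Trial period.** Study design says that the trial is performed "from June 2021 to June 2023".
- **Recruitment period.** Trial status says "Recruitment for the trial is planned to start on June 2021 and last until June 2023". It adds "The trial is enrolling patients"; the article was published in April 2022.
- **Primary outcome.** "The primary outcome of this study is the recurrence rate of CRA within 12 months" (Primary outcome).
- **When it is measured.** "the results of the electronic colonoscopy will be recorded at month 12" (Study design) and "the reexamine of colonoscopy will be undergone at month 12" (Study period).
- **Follow-up per patient.** The Discussion, which gives funding as the reason, says "our follow-up period is only 12 months".
- **Size.** "a total of 80 eligible patients will be enrolled" (Study design), 40 per group, with a 15% dropout assumption (Sample size).

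No section of the text gives a later date for the last follow-up visit.

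**The concern.** A trial that measures its primary outcome 12 months after entry needs at least 12 months between the last enrolment and the end of data collection. Here that interval is zero, because the same month closes both recruitment and the trial.

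Followed as written, the plan would cut off the only colonoscopy that determines the primary outcome for everyone enrolled in roughly the second year. Some would also miss the month-6 and month-3 visits. The article appeared about 10 months after the planned start, with enrolment still open, so the patients affected were still to come and the dates could still be corrected.

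**Working it through.** **Inputs.** Recruitment window A = 24 months (Trial status). Trial end T = 24 months after the start (Study design). Primary outcome at month 12, counted from the week-0 baseline (Study design, Study period). N = 80, allocated 1:1. Dropout assumption 15% (Sample size). The document gives no accrual curve, so the accrual pattern below is assumed.

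**Step 1: calendar.** Latest enrolment that allows a month-12 visit by June 2023: June 2023 − 12 months = June 2022. Month 12 for a patient enrolled in June 2023: June 2023 + 12 months = June 2024.

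**Step 2: the plan's own allowance.** The step from 66 to 80 is consistent with 66/0.85 = 77.6, rounded up to 78 and then to 80. The allowance is 0.15 × 80 = 12 patients. (Whether 66 follows from the stated formula is a separate question; the date conflict does not depend on it.)

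**Step 3: patients cut off under even accrual.** The share able to reach month m by the trial end is (T − m)/A.

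- Month 12: (24 − 12)/24 = 0.50, so 80 × 0.50 = 40 are cut off.
- Month 6: (24 − 6)/24 = 0.75, so 20 are cut off.
- Month 3: (24 − 3)/24 = 0.875, so 10 are cut off.

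Counting the end months whole changes the month-12 figure little. With T = 25 and A = 24, 80 × (1 − 13/24) = 36.7. With T = A = 25, 80 × (1 − 13/25) = 38.4. That is about 37 to 38.

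**Step 4: other accrual patterns.** If a share k enrols in the first 12 months, 80 × (1 − k) are cut off.

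| Share enrolled in first year | Without month-12 colonoscopy by June 2023 |
|---|---|
| 90% | 8 |
| 75% | 20 |
| 50% (even accrual) | 40 |
| 25% | 60 |

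The calendar loss alone exceeds the allowance of 12 whenever 80 × (1 − k) > 12, that is, when fewer than 85% (68 of 80) enrol in the first year. Ordinary dropout would come on top.

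**Step 5: precision.** Under even accrual and an equal split, 20 per arm could be assessed, or 20 × 0.85 = 17 after 15% dropout. Without the cut-off the figure would be 40 × 0.85 = 34; that is derived here and is not stated in the protocol. At the planning rates of 20% and 35%, the standard error of the difference is √[(0.20 × 0.80 + 0.35 × 0.65)/n] = √(0.3875/n). This gives 9.8 percentage points with n = 40 per arm and 13.9 with n = 20, a factor of √2 ≈ 1.41.

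**The case against.** The strongest reply is that the loss depends on a condition the document never states. No section says that follow-up or data collection stops in June 2023 for late enrollees. The month-12 colonoscopy is planned for every patient without exception. A loosely worded date in one section is at least as plausible as planned truncation. Study design also points to a project schedule in Figs. 1 and 2, which could not be seen for this check and may carry dates. This stands: the patient counts above are conditional. It does not remove the contradiction between the dates as printed.

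A reader might infer more than the document supports:

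- **That half is the most that could be lost.** It is the even-accrual figure. Later accrual gives more, earlier accrual less.
- **That patients without a month-12 colonoscopy would be counted as recurrence-free.** The Primary outcome formula divides by the number of patients in the group, but does not say that these are all randomised patients. The Withdrawal/dropout section lists incomplete clinical data and loss to follow-up, which points towards removal. The text does not settle the matter.
- **That a calendar cut-off would bias the comparison.** Allocation is random and 1:1, so a common calendar date falls on both arms alike. What is expected is lost precision.
- **That the blind could be broken too early.** Allocation concealment and blinding already ties unblinding to completion of the trial and data analysis, apart from emergencies. Database-lock rules and visit windows commonly sit in the full protocol or analysis plan, so their absence from the article is no fault.

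**Conclusion.** The inconsistency is real and rests on the document's own text. Study design and Trial status give identical dates for the trial and for recruitment, and these cannot both be exact alongside a month-12 primary outcome. The calendar result is firm: enrolment after about June 2022 is incompatible with a trial end in June 2023.

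The number affected is not firm. It needs two assumptions: that June 2023 is a hard stop, and how patients accrue. With both a hard stop and even accrual, about 40 of 80 would lack the primary outcome; across the accrual patterns shown, 8 to 60. Only the earliest-weighted pattern shown stays within the 12 that the dropout assumption allows. If one date is merely misreported and follow-up runs on to June 2024, no patient is lost to the calendar and only the text is wrong.

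**What to change.** Reconcile Study design and Trial status in one of two ways:

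1. Keep June 2023 as the end of the trial and end recruitment about June 2022; or
2. Keep recruitment to June 2023 and give about June 2024, the last patient's month-12 colonoscopy, as the end of study.

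Under either option the dates should let the final analysis follow every randomised patient's month-12 assessment.

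The cost is a date correction. Under the second option the trial also stays open for up to 12 more calendar months, but this only completes the follow-up already planned for each patient. The first option adds no calendar time, but all 80 patients must then be enrolled within about 12 months.

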## Data Availability

Supporting data regarding this study protocol can be obtained as supplementary data. [name], HW, and [name] will obtain the final trial data set and disclose the agreement. All individual participant data collected during the trial will be shared after identification.

## Abbreviations

TCM: Traditional Chinese medicine
CRAs: Colorectal adenomas
CRC: Colorectal cancer
JLJ granule: Jianpi Lishi Jiedu granule
EMR: Endoscopic mucosal resection
pEMR: Piecemeal endoscopic mucosal resection
ESD: Endoscopic submucosal dissection
